### Control group

The control ward will not receive the multimodal intervention and will continue with routine practice.

### Intervention group

The intervention will last 12 months and will be based on a theoretical model on effective knowledge mobilization, integrating a multimodal strategy related to peripheral catheters clinical practice improvement which includes the following (Fig. 1): (1) implementation of recommendations trough up-to-date protocols and posters related to hand hygiene and aseptic measures, insertion, maintenance and removal of PVC [34]; (2) use of e-learning technologies [35–37]; (3) feedback on the results and messages addressed to healthcare professionals to facilitate adherence to recommendations [38]; (4) face-to-face training sessions [39]. Masterclass related to PVC insertion, maintenance, and removal will consist of information shared about recommendation of CPGs adapted according to the needs detected by means of the questionnaire on the effectiveness of the healthcare practice; (5) leaflets with information for patients and family/careers about peripheral catheters, in appropriate language [40]; and (6) support by internal facilitators, which will be key members of staff in the organizations, to adopt best evidence based on the PARIHS theoretical model [26, 41, 42].

**Fig. 1 Fig1:**
[figure not shown]
Theoretical model on effective knowledge mobilization

This facilitation will be carried out by nurses using the Facilitating Implementation of Research Evidence (FIRE) approach, and who will flexibly tailor implementation strategies to the local ward context, and to resolve barriers and enablers identified. There will be two types of FIRE agents: hospital leaders (hFIRE) and hospital ward nurses (nFIRE). These agents will be allocated to the wards of each hospital. To mitigate the potential risk of facilitators leaving their posts during the study period we will deploy a co-facilitation model with three support nurses on each intervention ward. nFIRE nurses will be appointed to support and train other nurses on the GPC recommendations, carrying out the face-to-face training in their units, working in small groups to review process indicators and routines practices. Both nFIRE and hFIRE will lead an education program based on the theory of planned behavior [43–45] which includes behavioral techniques to facilitate the application of evidence-based practice. At the hospital level, the hFIREs will audit PVC-related practices, identifying barriers and providing support and guidance to resolve such hurdles. The facilitation strategy will be led by expert external facilitators, PREBACP group research, working with both types of FIRE.

### Data collection

To mitigate control bias, each nurse manager will be provided with information to standardize catheter removal, catheter tip culture, and hemoculture extraction. Tips from all PVC removed from patients experiencing adverse events will be cultured using a semiquantitative method. Clinical, microbiological, and ward information will be collected from each patient on PVC removal.

Project investigators will collect primary and secondary outcome data using a wide range of methods, including questionnaires NWI and EBPQ to nurses, clinical audits monthly, and clinical outcome by requesting statistics report the participating wards at each hospital with the variables. Where these data are not available, clinical outcome data will be adapted from our research to collect the primary and secondary outcome data. Tools will be used for communication between facilitators, auditors, and researchers to collect at the time of activity and throughout the duration of the intervention. The mean hospital length of stay for relevant wards will be collected as reported by the hospital electronic patient management systems. This data collection system was piloted in five of the above hospital units in December 2017. Adverse events will be defined as per international guidelines for the prevention of BSIs (Healthcare Infection Control Practices Advisory Committee, USA, UK, Spain) [46–48]. Three study phases will be planned for the PREBACP study: baseline (2 months), intervention and evaluation (12 months) (Fig. 2).

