### Secondary hypotheses

Nursing practice outcomes: An optimal fidelity of nurses to the recommendations within the CPG for insertion and management of peripheral venous catheter in hospital wards receiving the intervention will translate into reduced care variability, increased documentation about PVC use in nursing records and greater requests of catheter tip culture from PVCs removed from patients experiencing adverse events.Clinical outcomes: The fidelity of nurses to the recommendations within the CPG for insertion and management of peripheral venous catheter in hospital wards receiving the intervention will reduce unnecessary PVCs and decrease hospital length of stay (HLOS).Health economic outcomes: The implementation and development costs of the intervention will be offset by savings from decreased incidence of CRBSIs and HLOS.EBCP environment: The contextual and individual factors on the utilization of knowledge in clinical practice decisions and impact on hospital ward processes and practice measured by Nursing Work Index (NWI) [29] and Evidence-Based Practice Questionnaire (EBPQ) [30].

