### Secondary outcome measures: process evaluation

Nurses’ adherence to CPGs will be measured at 3, 6, 9, and 12 months with the following subcategories:1.1Multimodal intervention content will be delivered as planned (yes/no), and dosage will be delivered as often and long as planned (yes/no); face-to-face training session will be assessed by measuring the number of nurses who completed the Masterclass at the intervention phase. Feedback will be evaluated by checking the distribution of clinical audit results within intervention wards. Patient information will be assessed by monitoring the presence of informative leaflets on the ward (yes/no) and asking if the patient is aware of use of PVC and prevention recommendations for personal care. Facilitation will be measured by number of internal facilitators who completed the intervention.Clinical audits on use of PVC. Device utilization ratios will be measured by percentage of PVCs per hospital wards and number of PVC per patient. Documentation of PVC in nursing records will be assessed by percentage of fully completed records. PVC maintenance will be monitored by random, monthly clinical audits, which will document PVC size (16/18/20/22/24 gauge), site (dorsum of hand/forearm/antecubital region/upper arm), dressing integrity (clean/dry/intact), securement and time in situ (less 48 h/ between 48 and 96 h/more 96 h). Catheter tip will be measured by number of catheter tip extraction following removal of PVCs.Routine practice. Clinical effectiveness questionnaire for the prevention of PVC complications will be completed pre and post intervention. The questionnaire is made up of 35 questions in four sections, relating to general asepsis and skin antisepsis; PVC insertion, maintenance, and removal; PVC documentation; and patient and professional education.Clinical outcomes will be assessed using rates of unnecessary PVCs, rates of CRBSI, extravasation, obstruction and phlebitis, defined as per standard guidelines, and mean HLOS associated to PVC-BSIs at 3, 6, 9, and 12 months.The direct costs of implementing the multimodal intervention will be assessed using HLOS for patients and decrease rates of adverse events at 12 months (post intervention).EBCP environment:EBCP context: The contextual factors on the utilization of knowledge in clinical practice decisions and impact on hospital ward processes and practice will be assessed using the NWI tool pre-intervention. The variables are summarized into five main groups: nurses’ participation in hospital affairs; quality of nursing care; nurse management’s capacity, leadership, and support for nursing staff; size of the nursing workforce and adaptation of available human resources, and professional relation between doctors and nurses.EBCP individual: The opinions, attitudes, abilities and motivations of nurses and their links with the development of a culture of clinical practice based on the transfer of new knowledge to the healthcare given to patients will be assessed using EBPQ pre-intervention. The questionnaire is made up of 24 questions relating to professionals’ knowledge, use and attitudes towards EBCP.

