
### Sample size

Calculations are based on a previous observational pilot conducted in Manacor Hospital, which reported a global rate of 44.1% PVC-associated adverse events (16% phlebitis, 6.8% obstruction, 18.1% extravasation, and 3.2% CRBSIs rates of which 3.1% were CRBSIs type 1, 0.14% CRBSIs type 2, and none CRBSIs type 3). Similar studies have a potential for improvement between 7 and 19% in adverse event rates, such as phlebitis, infiltration, and obstruction, yet there is no statistical significance or potential for improvement in CRBSI rates [32, 33]. The initial assumption is for the intervention to decrease the rate of adverse events associated with PVC in the intervention group at 6 months post-intervention by 15%. For such target result, the sample size required would be 1920 nursing records, accepting an alpha risk of 0.05, a beta risk of 0.2 in a two-sided test, and 10% missing data. For the calculation of sample size, the smallest detectable difference with adequate power and statistical significance has been considered. The sample size has been corrected to account for within-intra cluster correlation coefficient of 0.01 to allow for a design effect of 1.99. The final sample size will therefore be of 3821 nursing records, assuming an average cluster size of 200 nursing records.

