### Data analysis

#### Effect evaluation and process evaluation

Quantitative methods will be used to analyze nursing practices, health service utilization, and economic outcomes. Main and secondary outcome analyses will be based on all randomized wards and selected participants. To account for within-patient correlation, due to multiple measurements from the same patient during assessment days, we will implement generalized estimating equation models with binary outcome and logic link for all rate outcome comparisons. The statistical analysis will consist of an exploration of the descriptive data of the sample, bivariate analysis with parametric and non-parametric tests, depending on the nature of the distributions (correlation, ANOVA, chi-square) and multivariate (multiple regression with independence analysis using Durbin-Watson statistics). The Cochran-Mantel-Haenszel test will be used to compare proportions. A series of exploratory analyses will be conducted on sub-groups and the impact of covariates on estimated of the effects of the intervention. A nonparametric median test will be used for HLOS comparison. In supportive analysis, HLOS will be considered as time to event data. Survival rates will be calculated and illustrated by the Kaplan-Meier method and further analyzed by the long rank test for univariate analysis. Variables that reveal prognostic or effect modifying potential on the outcome as suggested by univariate analysis will subsequently be evaluated by the proportional Cox regression for multivariate analysis. Hazard ratios with corresponding 95% confidence intervals will be reported. A *p* value of < 0.05 will be considered statistically significant. A regression model will be constructed to further explore the results obtained in the bivariate analysis, seeking to establish an explanatory model on the variables involved in improving the use of recommendations. Data will be analyzed using the program SPSS [name] Statistics version 21.

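### Length of stay is to be collected as ward means, which cannot supply the planned Kaplan-Meier, log-rank and Cox analyses, and the protocol describes the outcome in several incompatible ways

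*Protocol article*

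**What the plan says.** The protocol article deals with hospital length of stay (HLOS) in four sections.

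- **Secondary hypotheses.** Following the guideline is expected to shorten HLOS, with no restriction to infected patients. A further hypothesis expects savings from fewer catheter-related bloodstream infections (CRBSI) and shorter HLOS to offset the cost of the intervention.
- **Secondary outcome measures: process evaluation.** The clinical outcome is listed as "mean HLOS associated to PVC-BSIs at 3, 6, 9, and 12 months". The cost outcome in the same section uses patients' HLOS at 12 months, without mention of PVC-BSI.
- **Data collection.** "The mean hospital length of stay for relevant wards will be collected as reported by the hospital electronic patient management systems". The patient-level information named in this section is gathered when the catheter is removed. No admission date, discharge date or individual stay is listed.
- **Data analysis (Effect evaluation and process evaluation).** "A nonparametric median test will be used for HLOS comparison". Then: "In supportive analysis, HLOS will be considered as time to event data", and "Survival rates will be calculated and illustrated by the Kaplan-Meier method and further analyzed by the long rank test for univariate analysis". Cox regression follows, with hazard ratios and 95% confidence intervals.

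The Definitions section equates PVC-BSI with CRBSI type 3; types 1 and 2 have no positive blood culture. For the pilot, the Sample size section reports "none CRBSIs type 3".

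**The concern.** There are two linked problems.

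First, the unit of the data does not match the unit of the analysis. A Kaplan-Meier curve, a log-rank test and a Cox model each need a time and an event status for every patient. A ward mean holds neither. A later analysis plan can refine a model, but it cannot recover stays that were never extracted, so this has to be settled before the data request is made.

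Second, the sections differ in population (all patients, or those with PVC-BSI), in unit (patient or ward) and in summary (mean, median or time to event). A reader cannot tell which version tests the secondary hypothesis or feeds the cost result. One version, stay in patients with PVC-BSI, would be a poor basis for comparing arms. It selects patients by an event that occurs after randomisation and that the intervention is meant to prevent, and such patients are rare.

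**Working it through.** **Step 1. Which planned analyses can ward means support?**

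| Planned analysis of HLOS | Needs | Possible from ward means? |
|---|---|---|
| Median test | One value per unit compared | Yes, on 20 values (10 per arm if the 1:1 allocation is exact), but it compares ward averages |
| Kaplan-Meier, log-rank | Time and status per patient | No |
| Cox hazard ratios | Time, status and covariates per patient | No |

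**Step 2. Are the HLOS quantities the same?**

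| Section | Population | Quantity |
|---|---|---|
| Secondary hypotheses | Not restricted | HLOS, no summary named |
| Outcome list, clinical | Tied to PVC-BSI | Mean at four times |
| Outcome list, cost | Patients, not restricted | HLOS at 12 months |
| Data collection | Whole ward | Ward mean |
| Data analysis | Not restricted | Median test; time to event |

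No two rows agree in full.

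**Step 3. Where 3821 comes from.** The protocol gives no sample size for HLOS, so the planned number of nursing records is the available base. Inputs from the Sample size section: control rate 44.1%, reduction 15%, two-sided alpha 0.05, power 80%, missing data 10%, design effect 1.99.

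- Read as a relative reduction: 0.441 × 0.85 = 0.375.
- The two-proportion formula without continuity correction gives 866 per arm, 1732 in total.
- Allowing for missing data: 1732 / 0.9 = 1925, against 1920 stated.
- Clustering: 1920 × 1.99 = 3820.8, or 3821 as stated.

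The design effect is taken here as stated; whether it is right is a separate question.

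**Step 4. Expected PVC-BSI cases in 3821 records.** The Background section gives 0.1 to 0.5 per 1000 catheter-days. Catheter-days per record are not given, so they are an assumption, shown over a range.

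Expected cases = 3821 × days per record × rate / 1000.

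| Assumed days per record | Catheter-days | Cases at 0.1 | Cases at 0.5 |
|---|---|---|---|
| 2 | 7,642 | 0.8 | 3.8 |
| 3.5 | 13,373.5 | 1.3 | 6.7 |
| 5 | 19,105 | 1.9 | 9.6 |
| 7 | 26,747 | 2.7 | 13.4 |

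That is about 1 to 13 cases over both arms together. Even the top of the range is under one case per ward (13.4 / 20 = 0.67).

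**Step 5. How far the count depends on its base.**

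- If all catheter use on the 20 wards over 12 months were counted, exposure would be larger. Assuming 20 beds per ward with 40% of bed-days carrying a catheter, 20 × 20 × 0.4 × 365 = 58,400 catheter-days, giving 5.8 to 29.2 cases. Assuming 30 beds and 60%, 20 × 30 × 0.6 × 365 = 131,400 catheter-days, giving 13.1 to 65.7 cases. Bed numbers and percentages are assumptions.
- If all CRBSI types were meant, the pilot rate gives 3821 × 0.032 = 122 cases, but the Definitions section limits PVC-BSI to type 3.

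**The case against.** The strongest reply is that this is loose wording in a condensed article. The Setting section makes the ward the unit of analysis, so a nonparametric test on ward means can be run and respects the cluster design. The survival methods are labelled supportive, and HLOS is secondary. The electronic systems very likely hold individual stays. Data collection also mentions a range of methods and a fallback to the team's own data where hospital statistics are unavailable. Ward mean stays can be costed, and the cost outcome also uses adverse event rates.

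Much of this stands, and it limits the point. It does not remove it: the text names the ward mean as what is collected, the fallback does not mention individual stays, and the survival analyses are stated without the data they need.

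Four stronger readings are tempting, and the document does not support them.

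- *That no HLOS or cost result could be produced.* Ward means allow a comparison of ward averages and a cost calculation. Only the survival analyses are out of reach.
- *That the arms will be compared only among patients with PVC-BSI.* The outcome wording may mean descriptive or attributable stay, and the analysis text carries no such restriction. The conditioning problem applies only if that version is used to compare arms.
- *That in-hospital deaths will be mishandled in the time-to-discharge analysis.* The article is silent on this, and such rules are commonly left to an analysis plan.
- *That almost no PVC-BSI cases will occur.* The count rests on an assumed dwell time, on treating each record as one stretch of catheter use, and on 3821 as the base. The pilot's size is not given, so its zero sets no usable upper limit. The Discussion section itself acknowledges the low incidence.

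**Conclusion.** The point holds in limited form. Followed as written, the plan collects ward mean HLOS and so cannot deliver the Kaplan-Meier, log-rank and Cox results it announces; the median test would answer a question about ward averages. The sections also need to be reconciled on which HLOS is meant. Should the PVC-BSI version be used to compare arms, it would lose the protection of randomisation and rest on about 1 to 13 cases, assuming 2 to 7 catheter-days per record and 3821 records; with all ward catheter use counted, perhaps 6 to 66 under the exposure assumptions shown. The mismatch itself rests on the text and needs no assumption. The consequence is confined to a secondary outcome and the cost result that draws on it.

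**What to change.** 1. State one HLOS definition and use it in Secondary hypotheses, Secondary outcome measures, Data collection and Data analysis: the stay of all adult inpatients with a PVC on the 20 wards.
2. Replace the ward-mean report with a patient-level extract from the same electronic systems: admission date, discharge date, discharge status and ward.
3. Compare arms on these stays with a method that allows for clustering by ward, in both the main and the time-to-event analysis.
4. Report HLOS in patients with PVC-BSI as description only, with the number of cases.
5. Use the same patient-level stays in the cost outcome.

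One caution on step 1: the protocol also expects fewer unnecessary catheters, so having a PVC could itself shift between arms. Extracting stays for all adult inpatients of the 20 wards would allow a sensitivity analysis without that restriction.

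The cost is a larger data extract and revised wording. Randomisation, the intervention and the primary outcome do not change. The change is cheapest before the extract is requested.

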**Fig. 2 Fig2:**
[figure not shown]
Timeline of PREBACP study

### Definitions

CRSBI: The following case definitions will be used to determine a diagnosis of CRBSI (see Fig. 1):
▪CRBSI type 1: Local PVC-related infection (no positive blood culture): Positive quantitative culture (103 CFU/ml) or semi-quantitative culture with more than 15 CFU from the tip of PVC and local signs of infection at the insertion site or in catheter lumen.▪CRBSI type 2: General PVC-related infection (no positive blood culture positive): positive quantitative culture (103 CFU/ml) or semi-quantitative culture with more than 15 CFU from the tip of PVC and that clinical signs improve within 48 h of catheter removal.▪CRBSI type 3: PVC-BSI associated with microbiologically confirmed with blood culture occurring 48 h before or after catheter removal and positive quantitative culture (103 CFU/ml) or a semi-quantitative culture with more than 15 CFU from the tip of PVC for the same microorganism.
(b)Phlebitis: An inflammation of the wall of a vein. If a blood clot in the vein causes the inflammation, then the condition is termed thrombophlebitis. This problem is characterized by persistent pain referred to PVC (2 h since the last administration), erythema, swelling, and palpable thrombosis of the cannulated vein.(c)Extravasation: Inadvertent leakage of a vesicant solution into surrounding tissue.(d)Obstruction: Following occlusion of the PVC, which can be partial (i.e., blood cannot be aspirated, but PVC can be flushed) or complete, whereby neither aspiration nor infusion are possible.

### Data analysis

#### Effect evaluation and process evaluation

Quantitative methods will be used to analyze nursing practices, health service utilization, and economic outcomes. Main and secondary outcome analyses will be based on all randomized wards and selected participants. To account for within-patient correlation, due to multiple measurements from the same patient during assessment days, we will implement generalized estimating equation models with binary outcome and logic link for all rate outcome comparisons. The statistical analysis will consist of an exploration of the descriptive data of the sample, bivariate analysis with parametric and non-parametric tests, depending on the nature of the distributions (correlation, ANOVA, chi-square) and multivariate (multiple regression with independence analysis using Durbin-Watson statistics). The Cochran-Mantel-Haenszel test will be used to compare proportions. A series of exploratory analyses will be conducted on sub-groups and the impact of covariates on estimated of the effects of the intervention. A nonparametric median test will be used for HLOS comparison. In supportive analysis, HLOS will be considered as time to event data. Survival rates will be calculated and illustrated by the Kaplan-Meier method and further analyzed by the long rank test for univariate analysis. Variables that reveal prognostic or effect modifying potential on the outcome as suggested by univariate analysis will subsequently be evaluated by the proportional Cox regression for multivariate analysis. Hazard ratios with corresponding 95% confidence intervals will be reported. A *p* value of < 0.05 will be considered statistically significant. A regression model will be constructed to further explore the results obtained in the bivariate analysis, seeking to establish an explanatory model on the variables involved in improving the use of recommendations. Data will be analyzed using the program SPSS [name] Statistics version 21.

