### Setting

The study will be conducted in five public hospitals with diverse characteristics within the Spanish National Health System, including one reference hospital and four acute care hospitals. Twenty wards will be selected and randomly allocated to either the intervention or control groups. The intervention will be delivered at ward level, and therefore, the ward will be considered the unit of analysis. Emergency, critical care, pediatric, maternity, peri-operative, operative rooms, and psychiatric areas will be excluded from the analysis, due to the fact that peripheral catheters are routinely maintained inserted for less than 24 h. Bias-compensating measures will be incorporated to homogenize nursing practice through face-to-face training in excluded wards.

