### Randomization

Wards will be randomly allocated to the intervention or control arm using software, in blocks 1:1 with stratification by setting (medical or surgical) and hospital (to ensure homogeneity of both groups).

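### The adverse-event analysis of a ward-randomised trial is specified for within-patient correlation only, against the protocol's own statement that the ward is the unit of analysis

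*Protocol article*

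**What the plan says.** Four sections of the protocol article bear on this.

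- **Randomization:** the ward is the randomised unit, assigned 1:1 in blocks within strata formed by hospital and by medical or surgical setting.
- **Setting:** "Twenty wards will be selected and randomly allocated to either the intervention or control groups". Because the intervention is delivered at ward level, "the ward will be considered the unit of analysis".
- **Sample size:** the number of nursing records is "corrected to account for within-intra cluster correlation coefficient of 0.01", with a stated design effect of 1.99, an average of 200 records per ward and a final total of 3821.
- **Data analysis (Effect evaluation and process evaluation):** "To account for within-patient correlation, due to multiple measurements from the same patient during assessment days, we will implement generalized estimating equation models", and these are models "with binary outcome and logic link for all rate outcome comparisons". The same section lists chi-square and ANOVA, and states that "The Cochran-Mantel-Haenszel test will be used to compare proportions". It also plans a median test, log-rank test and Cox regression for length of stay, and "multiple regression with independence analysis using Durbin-Watson statistics".

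No analysis of adverse events is given a ward cluster, a ward random effect or a ward-level summary. The one model that includes the ward is the multi-level analysis of the nurse questionnaires, in the section on the evidence-based practice environment.

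**The concern.** Three sections treat the ward as the source of correlation that matters. The section that says how the arms will be compared names a different source, the patient, and stops there. Inflating the sample for clustering protects power. It does nothing for the validity of a test that ignores the clustering.

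If the analyst follows the data analysis section literally, the standard error of the arm difference omits the variation between wards. The primary p value and confidence interval would then not have their stated error rate and coverage.

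**Working it through.** **Inputs.** Sample size section: control rate 44.1%, 15% decrease, two-sided alpha 0.05, power 80%, 10% missing, 1920 records before clustering, ICC 0.01, design effect (DE) 1.99, 200 records per ward, 3821 in total. Setting section: 20 wards. Randomization section: 1:1, stratified by hospital and setting.

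**1. The plan's own figures.**
- A relative 15% decrease takes 44.1% to 0.441 × 0.85 = 37.5%. The usual two-proportion formula gives 866 per arm, 1732 in total, and 1732 / 0.9 ≈ 1925 (stated: 1920; an arcsine formula gives 1922). An absolute 15-point decrease would need only 358 and does not reproduce the figure.
- 1920 × 1.99 = 3820.8, which rounds to 3821, as stated.
- With DE = 1 + (m − 1) × ICC, m = 200 gives 1 + 199 × 0.01 = 2.99. The stated 1.99 requires m = 100.
- 3821 / 20 = 191 records per ward, which gives DE = 1 + 190.05 × 0.01 = 2.90.

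**2. Type I error if the ward is ignored.** The true standard error is √DE times the one used, so actual alpha = 2 × (1 − Φ(1.96 / √DE)).

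| Records per ward | DE | √DE | 1.96 / √DE | Type I error | Coverage of a nominal 95% interval |
|---|---|---|---|---|---|
| 100 (implied by the stated DE) | 1.99 | 1.41 | 1.39 | 16.5% | 83.5% |
| 191 (3821 / 20) | 2.90 | 1.70 | 1.15 | 25.0% | 75.0% |
| 200 (stated) | 2.99 | 1.73 | 1.13 | 25.7% | 74.3% |

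**3. Simulation.** The set-up was 20 equal wards, assumed to be four in each of five hospitals with two per arm, rate 44.1%, ICC 0.01 all between wards, and 40,000 runs. At 100, 191 and 200 records per ward:
- chi-square: 16.4%, 24.8%, 25.6%;
- Cochran-Mantel-Haenszel stratified by hospital: 16.4%, 24.9%, 25.6%;
- t-test on ward proportions: 4.9%, 5.2%, 4.9%.

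Stratifying Cochran-Mantel-Haenszel by ward is no way out, because each ward lies wholly in one arm.

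**4. What could lower the error.**
- *Several records per patient.* A patient-level GEE already carries a factor 1 + (k − 1)ρ for k records per patient with correlation ρ. The remaining inflation is [1 + (k − 1)ρ + (m − k) × 0.01] / [1 + (k − 1)ρ]. The protocol gives neither k nor ρ. Assuming k = 3 and ρ = 0.5: (2 + 0.97) / 2 = 1.485 at m = 100, error 10.8%; (2 + 1.97) / 2 = 1.985 at m = 200, error 16.4%. Over k = 1.5 to 3 and ρ = 0.1 to 0.5, the error is 11–16% at m = 100 and 16–25% at m = 200.
- *Half the ICC between hospitals.* Stratified randomisation balances that part. The simulated chi-square error is then 11.0% at 100 records per ward, 16.0% at 191 and 16.3% at 200.
- *Both at once*, with k = 3, ρ = 0.5 and an ICC of 0.005 left between wards: (2 + 0.485) / 2 = 1.24 at m = 100, error about 8%; (2 + 0.985) / 2 = 1.49 at m = 200, error about 11%.

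**5. Sensitivity to the ICC** at 200 records per ward, ward ignored: 0.001 gives 7%, 0.005 gives 17%, 0.02 gives 38%.

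**6. Durbin-Watson.** It tests correlation between adjacent rows, so its result depends on row order. Even with rows sorted by ward, an ICC of 0.01 gives a lag-1 correlation near 0.01 and a statistic near 2 × (1 − 0.01) = 1.98. Against a standard error of 1 / √3821 = 0.0162, a one-sided 5% test rejects with probability of about 1 − Φ(1.645 − 0.62) = 15%.

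**The case against.** The strongest defence is that the data analysis section gives a reason for using GEE and nowhere excludes the ward. The Setting section names the ward as unit of analysis, the Design section commits to the cluster extension of CONSORT, the data analysis section itself refers to all randomised wards, and a condensed article may leave the model to a fuller plan. This stands in part: one cannot say that the trial will be analysed without ward clustering. It does not remove the contradiction. The section is not silent on correlation. It names one source and omits the one that randomisation creates, and an analysis plan that followed it faithfully would inherit the gap. The Setting section names no method that would fill it.

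A reader might infer more than the documents support:
- *That every listed test is run on individual records.* The Data collection section says that mean length of stay is collected for wards, so the median test could be on ward values. Log-rank and Cox do imply individual data, but they are described as supportive.
- *That standard errors for all secondary outcomes are too small by the same factor.* The only ICC given is the sample-size one for adverse events, and the questionnaire analysis does model the ward.
- *That Durbin-Watson cannot detect clustering, or is offered as the check for it.* It is weak and depends on row order, but not blind, and the protocol attaches it to multiple regression rather than to the GEE.
- *That 16% is the least the error could be.* It rests on a design effect that does not follow from its inputs, and section 4 of the working shows plausible lower values.
- *That a false claim of efficacy is likely.* An inflated type I error does not make it so.

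**Conclusion.** The point holds as a contradiction. The data analysis section, as written, does not match the randomisation, the declared unit of analysis or the sample size correction, and this affects the primary p value and confidence interval.

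Its size is conditional on the section being followed literally and on the protocol's ICC of 0.01. On those terms, type I error is about 25–26% at 191–200 records per ward, the figure best supported by the protocol's own inputs, and 16.5% at the stated design effect. Either mitigating assumption alone could bring it to about 11% at the stated design effect, or about 16% at 191–200 records per ward. Both together would lower it further. All these values exceed the nominal 5%. Only a much smaller ICC than the protocol assumes would bring the error close to nominal.

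This needs to be corrected before analysis.

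**What to change.** Rewrite the data analysis section so that it agrees with the Setting, Sample size and Randomization sections:

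1. Make the ward the cluster for the primary outcome and the other arm comparisons, with patients and catheters nested within wards. Use a GEE clustered on ward or a mixed logistic model with a ward random effect, with a small-sample correction suited to 20 wards. A ward-level summary analysis is an alternative. It estimates a different quantity from a logistic model, so one should be named as primary.
2. Include hospital and medical/surgical setting. Ignoring them is conservative: in the simulation the unstratified ward-level t-test had 2–4% type I error when 25–50% of the ICC lay between hospitals.
3. Use ward-adjusted versions of any supporting analysis done on individual data (Cochran-Mantel-Haenszel, log-rank, Cox), and state for each whether the data are individual or ward-level.
4. Do not rely on Durbin-Watson as a check for ward clustering.

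This is a change of wording and needs no new data. The downside is wider but valid confidence intervals. By normal approximation, 3821 records give about 69% power at DE 2.90 and 67% at DE 2.99 (64% and 63% after 10% missing), against the planned 80%. That shortfall comes from the design effect in the sample size section. Ignoring the ward would hide it, not remove it.
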